## Abstract

Ulcerative Colitis (UC), a type of Inflammatory Bowel Disease (IBD), is a chronic, relapsing gastrointestinal condition with increasing global prevalence. The gut microbiome profile of people living with UC differs from healthy controls and this may play a role in the pathogenesis and clinical management of UC. Probiotics have been shown to induce remission in UC; however, their impact on the gut microbiome and inflammation is less clear. Anthocyanins, a flavonoid subclass, have shown anti-inflammatory and microbiota-modulating properties; however, this evidence is largely preclinical. To explore the combined effect and clinical significance of anthocyanins and a multi-strain probiotic, a 3-month randomised controlled trial will be conducted in 100 adults with UC. Participants will be randomly assigned to one of four groups: anthocyanins (blackcurrant powder) + placebo probiotic, probiotic + placebo fruit powder, anthocyanin + probiotic, or double placebo. The primary outcome is a clinically significant change in the health-related quality-of-life measured with the Inflammatory Bowel Disease Questionnaire-32. Secondary outcomes include shotgun metagenomic sequencing of the faecal microbiota, faecal calprotectin, symptom severity, and mood and cognitive tests. This research will identify the role of adjuvant anti-inflammatory dietary treatments in adults with UC and elucidate the relationship between the gut microbiome and inflammatory biomarkers in this disease, to help identify targeted individualised microbial therapies. ANZCTR registration ACTRN12623000630617.

## Introduction

Inflammatory Bowel Disease (IBD) is a chronic relapsing gastrointestinal disease encompassing both Crohn's Disease (CD) and Ulcerative Colitis (UC). Australia has one of the highest prevalence and incidence rates of IBD in the world, with approximately one in 250 Australians living with this disease, and an annual age-standardised incidence estimated at 29⋅3 new cases per 100 000 people.^(1,2)^ UC is characterised by inflammation in the mucosal cells of the colon, and can result in persistent gastrointestinal symptoms, fatigue, and extra-intestinal manifestations despite pharmaceutical management.^(3,4)^ Given the chronic and progressive nature of UC, the personal financial and quality-of-life costs, and the suboptimal response to medical management, effective dietary interventions that may alleviate the burden of this disease are urgently needed.^(3)^

Although the exact pathogenesis of UC is unclear, the widely accepted hypothesis involves an excessive immunological response to the intestinal microbiota and environmental factors in genetically susceptible individuals.^(5)^ Dysbiosis of the gut microbiome in people living with UC has been widely demonstrated, and is suggested to contribute to disease pathogenesis.^(6–8)^ Certain groups of beneficial gut bacteria are shown to be reduced in the gut microbiome of people with UC compared to healthy adults, particularly multiple species of butyrate-producing bacteria.^(6,9,10)^ The short-chain fatty acids (SCFAs) such as acetate, butyrate, and propionate, produced by the bacterial fermentation of non-digestible carbohydrates, have been shown to be significantly lower in adults with IBD compared to healthy controls.^(11,12)^ Of particular concern is the reduction in butyrate, which plays a significant role in maintaining intestinal barrier cells and regulating intestinal immune response.^(13,14)^ Due to difficulties in isolating and culturing butyrate-producing bacteria, they are not yet available as probiotic supplements.^(15)^ However, emerging research has identified a cross-feeding relationship between several *Bifidobacterium* and *Lactobacillus* species and butyrate-producing bacteria.^(16–19)^ Acetate, produced by *Bifidobacterium*, is a key intermediate for colonic butyrate production and acetate consumption has been commonly seen amongst butyrate-producing bacteria.^(20,21)^ Some butyrate-producing bacteria have also demonstrated the ability to utilise lactate in this cross-feeding relationship, lactate being a by-product of colonic fermentation by lactic acid bacteria including *Lactobacillus.*^(22)^ In this clinical trial, we propose supplementation with a probiotic blend containing multiple species of *Lactobacillus* and *Bifidobacterium* that have demonstrated anti-inflammatory benefits and result in increased production of butyrate SCFA.^(23–26)^

Probiotic supplementation has been shown to induce remission and reduce clinical disease activity in populations with UC. A recent systematic review and meta-analysis synthesising data from 37 IBD trials has found that probiotic supplements containing 2–3 (or more) different strains of *Lactobacillus* or *Bifidobacterium*, and administered at a daily dose of 10^9^–10^12^ colony-forming unit (CFU)/day were able to induce disease remission, particularly in UC, and proliferate *Bifidobacterium* and *Lactobacillus* in the gut microbiota of participants.^(27)^ Another recently published systematic review and meta-analysis found that, of 25 studies amongst adults with UC, 21 showed probiotics to be effective in achieving or maintaining remission. Supplementation with *Bifidobacterium sp.* or a combination of probiotics was the most effective intervention compared to control.^(28)^

It is established that anthocyanins, a polyphenol subclass found in red-, blue- and purple-coloured fruits and vegetables,^(29)^ exert anti-inflammatory effects and interact with the gut microbiome, and therefore may be beneficial adjuvant treatments in UC.^(30)^ There are multiple preclinical studies supporting the anti-inflammatory benefits of anthocyanin supplementation in populations with UC.^(31)^ This evidence is largely obtained from animal and laboratory models, and therefore further clinical trials are necessary to provide translational evidence. Evidence from animal and *in vitro* studies suggests that polyphenols, including anthocyanins, function as prebiotics in the gut microbiota and can stimulate the growth of beneficial microbes including those shown to be lacking in adults with UC.^(32–35)^ The increase in beneficial gut microbes and consequent production of metabolites, including SCFAs, has been shown to reduce inflammatory biomarkers.^(34,35)^ What remains unclear is whether and how probiotic supplementation enriched with anthocyanins influences disease activity, inflammation and the gut microbiome in UC.

We have identified a significant gap in the literature pertaining to a lack of clinical trials and data that test if there are changes to both inflammatory markers and the gut microbiota profile after supplementation with microbiota-modulating therapies in UC. Both polyphenols and probiotics have been shown to reduce inflammation, however the magnitude may not be clinically significant in this population.^(36–38)^ Thus, we aim to test, for the first time, whether the combination of these two separate interventions results in synergistic effects with a greater magnitude of change to intestinal inflammation and therefore beneficial disease control. We additionally aim to assess whether changes in inflammation and the gut microbiota are associated with an improved quality of life and a reduction in symptom burden.

### Research aim and objectives

This study aims to evaluate the combined effect and clinical significance of a multi-strain probiotic intervention (VSL#3®^,^ containing one strain of *Streptococcus thermophilus*, three strains of *Bifidobacterium* and four strains of *Lactobacillus*) provided together with dietary anthocyanins extracted from New Zealand-grown blackcurrants on the gut microbiota profile and inflammatory biomarkers in adults with UC.

We hypothesise that (1) anthocyanins, in combination with probiotics, will result in a reduction in gut inflammation measured by faecal calprotectin (FCAL) and will modulate the gut microbiome measured through shotgun metagenomic sequencing of faecal samples; (2) anthocyanins, in combination with probiotics, will result in a synergistic effect that results in a significantly greater reduction in FCAL and improvement in the gut microbiome than each intervention alone; (3) the reduction in FCAL will be explained by beneficial changes to the gut microbiome profile; and (4) these changes in FCAL and the gut microbiome will lead to clinically significant improvements in health-related quality-of-life measured with the IBDQ-32.

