### Inclusion and exclusion criteria

Inclusion criteria: (1) diagnosis of UC for at least 3 months prior to screening, documented by endoscopic and histologic findings; (2) aged ≥18 years; (3) willing and able to take oral supplements; (4) able to communicate in the English language.

Exclusion criteria: (1) CD; (2) change in antibiotics or probiotics in past 3 months, including commencing antibiotics/probiotics, ceasing antibiotics/probiotics or changing the type of antibiotic/probiotic consumed; (3) escalation to biologics or immunomodulators in the past 6 weeks; (4) currently taking steroids >20 mg daily; (5) bowel resection surgery; (6) pregnant and lactating women; (7) end-stage liver or kidney failure; (8) current treatment for *Clostridium difficile* or other intestinal infection; (9) sucrose-isomaltose deficiency or maltose intolerance.

As per the Medical Advisor's recommendation, all participants must have stable medication for 2 weeks prior to commencing the study. All types of IBD medications are permitted in this study. Participants who have taken antibiotics or probiotics consistently for 3 months prior to recruitment will be permitted to commence the study, provided they agree to continue taking the probiotic/antibiotics throughout the study. Patients receiving topical therapy (enemas or suppositories) are eligible to participate if they are willing to continue the therapy at a stable dose throughout the study. Participant receiving steroids >20 g/day can commence the study 2 weeks after their dosage has reduced to ≤20 mg/day. Participants treated with steroids ≤20 mg/day are eligible to participate if they plan to maintain this stable dose for all the study duration.

Participants who require a change in their medication treatment related to uncontrolled UC activity (i.e. increase in steroids or mesalamine doses, start of steroids or biologics or immunosuppressants) during the 12-week intervention, those who do not comply with the study protocol, and those who voluntarily leave the study will not be included in the per-protocol analyses. These participants will be encouraged to continue to complete required outcome data and attend the final visit for inclusion in the intention-to-treat (ITT) analysis.

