#### Faecal calprotectin

FCAL will be measured at baseline and 12 weeks. FCAL is a sensitive marker of intestinal inflammation and has been shown to correlate to histological and endoscopic inflammation and disease activity measures.^(54,55)^

Faecal samples for FCAL will be collected in an ELISA kit (Epitope Diagnostic) and stored at −80 °C until all samples are collected. FCAL will be determined with a range of 0–321 μg/g or 0–892 ng/ml calprotectin. The analytical sensitivity (LLOD) of the human calprotectin ELISA as determined by the 95 % confidence limit on 12 duplicate determination of zero standard is approximately 2⋅5 ng/ml. A LLOQ was determined by dilution of assay standards and it is approximately 5 ng/ml.

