### Statistical analysis

Statistical analyses will be performed in Stata software,^(65)^ R software^(66)^ and/or IBM SPSS Statistics.^(67)^ An ITT analysis will be the primary analysis, including all participants randomised and analysed according to the treatment group to which they were originally assigned. A per-protocol analysis will additionally be conducted for all outcomes and used as a sensitivity analysis compared to the ITT. The per-protocol analysis will include participants who completed the trial without major violation including medical disruptions or unblinding, and who exhibited >80 % compliance to the intervention products.

Baseline demographics and measurements will be reported for each intervention group as means and standard deviations or 95 % CI.

The primary outcome will be the mean IBDQ-32 score at week 12 adjusted for baseline and covariates and assessed using an ANCOVA. A sensitivity analysis of differences in within-group change in IBDQ-32 score from baseline to week 12 will be measured using a two-sample *t*-test or Mann–Whitney *U*-test depending on normality of distribution. Within-group differences in secondary outcomes measured at two timepoints will be evaluated using a two-sample *t*-test or Mann–Whitney *U*-test depending on normality of distribution. Within-group differences in secondary outcomes measured at three time points will be evaluated using linear mixed modelling. Between-group differences of outcomes will be explored using ANOVA or ANCOVA if covariates need to be considered or mixed models. Relevant covariates associated with the primary outcome of health-related quality-of- life will be included in the analyses. Secondary analyses will be conducted to investigate relationships between changes in outcome measures. Predictors and assumptions of missing data will be investigated. Methods such as multiple imputation will be considered depending on the data missing. Appropriate sensitivity analyses will be performed.

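### Hypothesis 1 names no comparator and the plan does not say which analysis decides it, so a spontaneous fall in FCAL within the combination arm could be reported as a treatment effect

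*Protocol article*

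**What the plan says.** **The hypotheses (Protocol article, Research aim and objectives).** Hypothesis 1 is that anthocyanins in combination with probiotics "will result in a reduction in gut inflammation measured by faecal calprotectin (FCAL) and will modulate the gut microbiome". No arm is named for comparison. Hypothesis 2 does name comparators: it expects a "significantly greater reduction in FCAL and improvement in the gut microbiome than each intervention alone". Those comparators are the single-agent arms. Hypotheses 3 and 4 start from the FCAL and microbiome changes and name no control. The double placebo, arm 4 of the trial, appears in none of the four.

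**The measurements (Faecal calprotectin; Secondary outcome measures).** "FCAL will be measured at baseline and 12 weeks", and metagenomic sequencing follows the same two-point schedule.

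**The analysis (Statistical analysis).** "Within-group differences in secondary outcomes measured at two timepoints will be evaluated using a two-sample" t-test or a Mann–Whitney U-test. Then: "Between-group differences of outcomes will be explored using ANOVA or ANCOVA", the latter if covariates are needed, or mixed models. No contrast is named and no test is tied to hypothesis 1. The primary outcome, by contrast, is fixed as week-12 IBDQ-32 adjusted for baseline by ANCOVA.

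**The setting.** The Introduction says that inflammatory bowel disease, of which UC is one form, "is a chronic relapsing gastrointestinal disease". Under Inclusion and exclusion criteria, "all participants must have stable medication for 2 weeks prior to commencing the study". Escalation to a biologic or immunomodulator excludes a person only within the past 6 weeks, and entry is possible 2 weeks after a steroid reduction.

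**The concern.** A change from baseline in one arm mixes the treatment effect with everything else that moves FCAL over 12 weeks: the natural course of a relapsing disease, background therapy changed shortly before entry, and chance timing of enrolment. The randomised double-placebo arm is there to remove these influences, but hypothesis 1 does not call on it.

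A significant fall within the combination arm could therefore be presented as confirming hypothesis 1 even if the placebo arm fell just as far. Reading the arms side by side (significant with the combination, not significant with placebo) would not repair this, because that pattern is not a test of the difference. Hypotheses 3 and 4 take the FCAL reduction as their starting point, so a wrong conclusion on hypothesis 1 would carry into both.

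This is separate from the question of which test suits paired data. A correct paired test would still leave spontaneous change and treatment effect together.

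**Working it through.** **1. Inputs.**
- Arm sizes from Sample size and power calculations: 19 evaluable and 25 recruited per arm. They were derived for IBDQ-32 and are used here only as arm sizes. The documents give no figure for FCAL to reproduce.
- For the record, 19 does not reproduce as a two-arm comparison at effect size 0.8 and 95% power, which needs 35 per arm one-sided or 42 two-sided. It matches a one-sided one-sample or paired test (18.4, rounded up to 19). That is a separate matter about the primary outcome, and nothing below depends on it.
- Assumptions: treatment effect zero; spontaneous mean improvement δ of 0.2 to 0.5, in units of the SD of the change, the same in every arm; two-sided α of 0.05. The documents give neither an FCAL SD nor an expected drift.

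**2. Within-arm paired test.** The rejection probability q comes from the noncentral t distribution with n − 1 degrees of freedom and noncentrality δ√n. For δ = 0.5 and n = 25 the noncentrality is 0.5 × 5 = 2.5, which gives q = 0.670.

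| δ (assumed) | q, n = 19 | q, n = 25 |
|---|---|---|
| 0.2 | 0.131 | 0.161 |
| 0.3 | 0.236 | 0.302 |
| 0.4 | 0.379 | 0.484 |
| 0.5 | 0.541 | 0.670 |

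**3. One arm significant, the other not.** With no treatment effect, the chance that the combination arm is significant and the placebo arm is not is q(1 − q). The smallest value is 0.131 × 0.869 = 0.114 (n = 19, δ = 0.2). The largest is 0.484 × 0.516 = 0.250 (n = 25, δ = 0.4). The range is 11–25%.

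**4. Between-arm test.** Equal drift cancels in the difference between arms. In a simulation of 20,000 trials per setting, a t-test of change, combination versus double placebo, rejected in 4.7–5.3% of trials at every drift examined (0 to 0.8).

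**5. The test the plan names.** A two-sample t-test of baseline against week 12 ignores the pairing, so its rate depends on the correlation ρ between the two measurements, also not given. Simulated rejection rates with no treatment effect:

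| δ, n | ρ = 0.3 | ρ = 0.5 | ρ = 0.7 |
|---|---|---|---|
| 0.2, n = 19 | 7.0% | 3.1% | 0.6% |
| 0.2, n = 25 | 8.9% | 4.2% | 0.9% |
| 0.5, n = 19 | 41% | 27% | 9.3% |
| 0.5, n = 25 | 55% | 38% | 15% |

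Each is below the paired rate in step 2. At the small drift with ρ of 0.5 or more it is below 5%; at the larger drift it exceeds 5% throughout.

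**The case against.** The strongest reply is that the plan does not rest on within-arm tests alone. The sentence on between-group differences covers outcomes without restriction, so it includes FCAL. Wording that a treatment results in a reduction is causal and, in a double-blind trial with a double-placebo arm, can be read as relative to control. Hypothesis 2 requires between-arm comparisons, and the sample size section names combination versus control as the comparison of interest, though for IBDQ-32. FCAL and the microbiome are secondary, and a condensed article may leave the pairing of each hypothesis with its contrast to a fuller document.

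Much of this stands, and it rules out some tempting inferences:

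- A reader might infer that hypothesis 1 is by definition a before-to-after claim tested only within arm. The text does not say so. It leaves the comparator open and plans both kinds of analysis.
- A reader might take the choice of verbs, evaluated for within-group and explored for between-group, as a declared hierarchy. No hierarchy is stated.
- A reader might infer that spontaneous improvement would be reported as benefit. It could be. No drift is documented and its direction is unknown: FCAL may also rise, and a within-arm test could then hide a real effect. Entry sets no minimum disease activity or FCAL, so the criteria do not select people in a flare.
- A reader might take 13–67% as the plan's own error rate. It assumes a paired test that the plan does not name.

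What the reply does not remove is that the article is not silent here. It states the hypothesis without a control, assigns these outcomes a within-group significance test, and leaves the deciding analysis open.

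**Conclusion.** The point holds in this limited form: hypothesis 1 has no comparator, no FCAL or microbiome hypothesis names the double placebo, and the analysis section leaves room for a within-arm p-value to decide the question. The trial has the right control arm and a between-group analysis is planned. The defect is that neither is made decisive.

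The size is illustrative. It rests on an assumed improvement of 0.2 to 0.5 SD common to all arms, no treatment effect, and a correct paired test. With the named two-sample test the excess ranges from none to large, depending on drift and correlation. The conclusion that only the between-arm contrast separates treatment from spontaneous change does not depend on those figures. The matter concerns secondary outcomes, but they carry the trial's stated aim, so the change is worth making before analysis.

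**What to change.** 1. Restate hypothesis 1 as a greater reduction in FCAL, and a greater change in whichever microbiome measure the analysis plan designates, with the combination than with double placebo.
2. Decide it by the between-arm difference at week 12 adjusted for baseline, using the ANCOVA already planned for the primary outcome.
3. Report within-arm changes descriptively with confidence intervals and without p-values, and state that they support no efficacy claim.

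This alters one hypothesis and two sentences of the Statistical analysis section and needs no new data. The price is that significance is harder to reach. Unadjusted, the standard error of a difference between two arms is √(2/n) ÷ √(1/n) = √2, about 1.4 times that of one arm's mean change. For a true effect of 0.8 SD of the change with no drift, 19 per arm give about 67% power between arms, against 91% for a paired within-arm test (two-sided 0.05). With 25 per arm the figures are 79% and 97%. Baseline adjustment may recover some of this, by an amount that depends on a correlation the documents do not give.

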## Methods

This is a double-blind randomised controlled trial protocol for examining the effectiveness of anthocyanins alone, and in combination with a multi-strain probiotic, over 3 months for adults aged ≥18 years with UC. One hundred eligible participants will be randomly assigned to one of four intervention arms in a 1:1:1:1 ratio for a 3-month duration: (1) 310 mg of anthocyanin derived from New Zealand blackcurrants with a placebo probiotic; (2) multi-strain probiotic with a placebo fruit powder; (3) 310 mg anthocyanin plus a multi-strain probiotic; (4) double placebo. Written informed consent will be obtained from all participants prior to commencing the trial.

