#### Sample size and power calculations

Our sample size (*n* 100) was calculated in G*Power Version 3.1.9.6 based on the primary outcome measure of a clinically relevant change in mean score of ≥16 in the 32-item Inflammatory Bowel Disease Questionnaire (IBDQ-32).^(39,40)^ The primary comparison of interest is between the combined intervention versus control. Assuming a mean change in the IBDQ-32 score of 16 ± 20 estimated from previous literature,^(41–44)^ α- significance of 0⋅05 and power 95 %, a sample size of n 19 per arm is required with effect size of 0⋅8. To allow for ~25 % drop-out, given the duration of this trial and based on previous literature,^(45–47)^
*n* 25 participants will be recruited to each arm.

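### Hypothesis 2 expresses synergy as the combination beating each product alone, which purely additive effects also achieve, and no interaction contrast is named

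*Protocol article*

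**What the plan says.** The Introduction states that the trial will test "whether the combination of these two separate interventions results in synergistic effects with a greater magnitude of change to intestinal inflammation". Hypothesis 2, under Research aim and objectives, says what that is expected to look like: a "synergistic effect that results in a significantly greater reduction in FCAL and improvement in the gut microbiome than each intervention alone".

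Under Methods, participants are "randomly assigned to one of four intervention arms in a 1:1:1:1 ratio for a 3-month duration": anthocyanin with placebo probiotic, probiotic with placebo powder, both products, or double placebo. The word factorial is not used, but these are the four cells of a 2x2 layout.

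Under Sample size and power calculations, "The primary comparison of interest is between the combined intervention versus control", and it is sized on IBDQ-32 alone. Under Statistical analysis, "The primary outcome will be the mean IBDQ-32 score at week 12 adjusted for baseline and covariates and assessed using an ANCOVA". For the other outcomes, "Between-group differences of outcomes will be explored using ANOVA or ANCOVA if covariates need to be considered or mixed models". No section names an anthocyanin-by-probiotic term or any contrast that measures departure from additivity.

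**The concern.** Synergy means that the two products together do more than the sum of what each does alone. Being better than each product alone is a weaker property. If both products work and their effects add, the combination is better than either by construction, with no interaction at all. It can even be better than either when the products partly cancel each other.

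This case is realistic here. The Introduction says that polyphenols and probiotics have each been shown to reduce inflammation, although perhaps not by a clinically relevant amount. Two individually active products are therefore the protocol's own premise, and that is the setting in which the criterion in hypothesis 2 misleads.

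At stake is the interpretation of the FCAL and microbiome results. A significant win over both single arms could be published as synergy when the data show only addition. Failure to win would say little about synergy either way.

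**Working it through.** **Inputs.** From Sample size and power calculations: "Assuming a mean change in the IBDQ-32 score of 16 ± 20 estimated from previous literature", hence SD 20 and a standardised effect of 16/20 = 0.8; 19 evaluable and 25 recruited per arm; "significance of 0⋅05 and power 95" per cent. The article gives no effect or SD for FCAL or the microbiome, so the IBDQ-32 SD stands in as an illustration. Single-product effects of 10 points (0.5 SD) and 16 points (0.8 SD) are assumptions.

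**The plan's own figure.** A two-sample t-test at 0.8 SD, two-sided 0.05 and 95% power needs 42 per arm (35 one-sided), not 19. A one-sided paired or one-sample test does give 19 (power 95.6%). That is a separate matter; 19 and 25 serve here only as arm sizes.

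**Criterion against definition.** Let the mean benefits over double placebo be a (anthocyanin), p (probiotic) and a + p + i (combination), where i is the interaction.

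- Combination minus anthocyanin = p + i.
- Combination minus probiotic = a + i.
- Synergy contrast: combination − anthocyanin − probiotic + double placebo = i.

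With i = 0 and both products active, the first two differences are positive and the third is zero. The first two also stay positive for negative i, as long as |i| is smaller than both a and p.

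**How often additive effects meet the criterion.** Simulation with i = 0, equal single-product effects, and the combination required to be significantly better than both single arms (each test two-sided 0.05):

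| Each product adds | 19 per arm | 25 per arm |
|---|---|---|
| 10 points (0.5 SD) | about 18% | about 25% |
| 16 points (0.8 SD) | about 52% | about 67% |
| Positive interaction test, either effect | about 2.5% | about 2.5% |

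The first two rows move by one or two percentage points according to whether the variance is pooled over all four arms or estimated from each pair. With pooling, 0.8 SD gives 53.7% and 68.9%. Over a wider assumed range, also pooled, the rate runs from 10.7% (0.4 SD each, 19 per arm) to 97.7% (1.2 SD each, 25 per arm).

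**Precision of the right contrast.** Its variance is 4 × SD²/n, so its SE is 2 × SD/√n.

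- 19 per arm: 2/√19 = 0.46 SD. On the IBDQ-32 scale, 0.459 × 20 = 9.2 points; the 95% CI half-width is 1.99 × 9.18 = 18.3 points. The interaction detectable with 80% power is about 1.3 SD (26.1 points).
- 25 per arm: 2/√25 = 0.40 SD. The detectable interaction is about 1.13 SD (22.6 points).
- Power for an interaction of 0.8 SD is 40.5% and 50.8% respectively. With an assumed baseline correlation of 0.5 to 0.7, baseline adjustment raises the 19-per-arm figure to 51% to 67%.
- Without baseline adjustment, 80% power for 0.8 SD needs 50 per arm.

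**The case against.** **The analysis may already allow for it.** ANOVA, ANCOVA and mixed models can all carry two factors and their interaction, and model terms for secondary outcomes are often left to a full protocol or SAP, which is not shown. This stands in part. A reader might infer that the plan cannot answer the synergy question, but nothing in Statistical analysis excludes a two-factor model. What a later document would not repair by itself is the criterion worded in hypothesis 2: an SAP that follows it would carry the error forward.

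**Synergy is not the trial's central claim.** This stands. The stated aim is the combined effect and its clinical significance. Synergy is one of four hypotheses and concerns secondary outcomes, although the Introduction also names it as an aim. The primary contrast is untouched.

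**The article has no rule for declaring synergy.** Hypothesis 2 can be read as offering synergy as the mechanism and the greater reduction as its consequence. A reader might conclude that additive effects would be reported as synergy; the article supports only that they could be. Even on the milder reading, the sole observable sign given for synergy is one that additivity also produces.

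**The size is easily overstated.** Counting a win over just one single arm gives 32% to 41% (10 points) and 67% to 79% (16 points). These are not the relevant rates, because the hypothesis says each product, so both must be beaten. All the figures are also on IBDQ-32, for which no synergy is hypothesised.

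**Conclusion.** The concern holds in a limited form. The criterion in hypothesis 2 cannot separate synergy from addition, and no stated analysis supplies the contrast that would. In the IBDQ-32 illustration, purely additive products meet the criterion in about 18% to 25% of trials (10 points each) or 52% to 67% (16 points each), against about 2.5% for a positive result on an interaction test.

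These rates rest on equal single-product effects, SD 20, zero interaction, normal data and no baseline adjustment. They are not estimates for FCAL or the microbiome, for which the article gives no inputs. That additive effects satisfy the criterion does not depend on any of these numbers.

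The documents do not support the stronger readings: that the trial as a whole rests on synergy, that its data could not address it, or that a false claim is certain. The 2x2 layout lets the interaction be estimated from the planned arms, only imprecisely.

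**What to change.** 1. For FCAL, prespecify the baseline-adjusted contrast combination − anthocyanin − probiotic + double placebo, reported with its 95% CI, as the only test of synergy and labelled exploratory.
2. Name the scale. Effects that add on the raw scale do not add on the log scale, so the choice (log, for example) decides what counts as synergy. State how values beyond the assay range given under Faecal calprotectin (0–321 μg/g) are handled, since truncation there can distort an interaction.
3. Reword hypothesis 2 so that superiority over each product alone is stated as just that and not called synergy.
4. State the precision: SE 0.46 SD at 19 per arm, and a detectable interaction of about 1.3 SD at 80% power before baseline adjustment.

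Combination versus double placebo on IBDQ-32 stays as the primary comparison. Main effects pooled over the other product, and an interaction for IBDQ-32, are optional; pooled main effects are cleanly interpretable only if there is no interaction.

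The cost is one contrast and some wording, with no extra participants or assessments. The downside is that the plan must say openly that a trial of this size can say little about synergy unless it is very large.
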